### Blinding

Health care professionals and participants will be aware of the allocation arm but blinded to the results of any former assessment. Health care professionals who are outcome assessors will be blinded to participants’ allocation.

### Sample size

Assuming 70% or more of the participants in the TPA group and 43% of the participants (estimate based on previous data) in the REF group would return to work during the 3-month period of observation, a sample size of 46 individuals in each group will be required to achieve greater than 80% statistical power (two-sided, alpha = 0.05). The eleven time sequences of enrollment are required to recruit this number of participants.

Prospectively, this study will not be powered with a pre-hoc assumption of superiority or non-inferiority between the TPA and CPSMP groups. The CPSMP group is included as an active comparator.

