**Methods:**

This protocol describes the design of a parallel randomised controlled trial on the efficacy of ‘Tailored Physical Activity’ or a ‘Chronic Pain Self-management Program’ versus a reference group for sick-listed citizens with complaints of pain in the back or upper body. Participants will have been absent from work due to sick-listing for 3 to 9 weeks at the time of recruitment. All interventions will be performed at the ‘Health Care Center’ in the Sonderborg Municipality, and a minimum of 138 participants will be randomised into one of the three groups.

All participants will receive ‘Health Guidance’, a (1.5-hour) individualised dialogue focusing on improving ways of living, based on assessments of risk behavior, motivation for change, level of self-care and personal resources. In addition, the experimental groups will receive either ‘Tailored Physical Activity’ (three 50-minute sessions/week over 10 weeks) or ‘Chronic Pain Self-Management Program’ (2.5-hours per week over 6 weeks). The reference group will receive only ‘Health Guidance’.

The primary outcome is the participants’ sick-listed status at 3 and 12 months after baseline. The co-primary outcome is the time it takes to return to work. In addition, secondary outcomes include anthropometric measurements, functional capacity and self-reported number of sick days, musculoskeletal symptoms, general health, work ability, physical capacity, kinesiophobia, physical functional status, interpersonal problems and mental disorders.

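### 46 per group gives about 75% power for 70% versus 43%, not the stated more than 80%

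*Protocol article*

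**What the plan says.** The Sample size section of the protocol article gives every input. The event proportions are introduced by "Assuming 70% or more of the participants in the TPA group and 43% of the participants (estimate based on previous data) in the REF group", and the outcome is return to work within the 3-month observation period. The section then concludes that "a sample size of 46 individuals in each group will be required to achieve greater than 80% statistical power (two-sided, alpha = 0.05"). It says that no comparison between TPA and the Chronic Pain Self-Management Program (CPSMP) is powered, so the power claim concerns TPA versus REF only.

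The Abstract (Methods) states that "a minimum of 138 participants will be randomised into one of the three groups". That total is 3 × 46 = 138, so it holds no allowance above the calculated number. The Statistical analysis section names a chi-squared test for the primary outcome and mentions no continuity correction.

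**The concern.** The three elements of the sample-size statement (the two proportions, the two-sided 5% level and 46 per group) fix the power. That power falls short of 80% under every two-sided method for two proportions that was tried.

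This is the only comparison for which power is claimed, and the claim is what a reader will use to interpret a negative result. If the trial is believed to have more than 80% power for a 27-point difference, a non-significant result looks like fair evidence against a difference of that size. With a type II error of about 25%, or about 33% under a corrected or exact test, that reading is too strong.

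**Working it through.** **Inputs, all from the protocol article.** p1 = 0.70 (TPA) and p2 = 0.43 (REF), two-sided alpha 0.05, n = 46 per group, stated power above 80% (Sample size); chi-squared test (Statistical analysis).

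Derived quantities:
- difference d = 0.27, d² = 0.0729
- mean proportion = 0.565; pooled term √(2 × 0.565 × 0.435) = 0.7011
- unpooled variance sum 0.70 × 0.30 + 0.43 × 0.57 = 0.4551; its root = 0.6746
- normal quantiles 1.96 and 0.8416; (1.96 + 0.8416)² = 7.849

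**Attempt to reproduce 46 per group with more than 80% power.**

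1. Pooled variance, which corresponds to the uncorrected chi-squared test.
   - n for 80% = (1.96 × 0.7011 + 0.8416 × 0.6746)² / 0.0729 = 51.7, so 52.
   - Power at 46 = Φ[(0.27 × √46 − 1.96 × 0.7011) / 0.6746] = Φ(0.678) = 75.1%.
   - Power at 52 = 80.2%.
2. Exact enumeration of the uncorrected chi-squared test over both binomial distributions: 74.3% at 46.
3. Unpooled variance, the most favourable.
   - n = 7.849 × 0.4551 / 0.0729 = 49.0.
   - Power at 46 = Φ[0.27 / √(0.4551/46) − 1.96] = 77.5%.
4. Arcsine transformation: n = 51.5, so 52; power at 46 = 75.4%.
5. Continuity correction: n = (51.73/4) × [1 + √(1 + 4/(51.73 × 0.27))]² = 58.9, so 59. Exact power of the Yates-corrected test and of Fisher's test at 46 is 67.1%.

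The stated figure is not reproduced. Two-sided power at 46 lies between 67.1% and 77.5%.

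**Readings the text does not state.**

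- One-sided 5% test: 84.3% at 46, with 41 per group needed for 80%. The Sample size section says "two-sided, alpha = 0.05", so this is not the stated calculation.
- Log-rank test, assuming exponential times to return to work: hazard ratio = ln(0.30)/ln(0.57) = 2.14; expected events = 46 × (0.70 + 0.43) = 52; Schoenfeld power = 78.4%. About 48 to 49 per group would be needed.
- Chi-squared test across all three groups (2 degrees of freedom), taking the CPSMP rate, which the plan does not give, anywhere from 43% to 70%: 64% to 79%.

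**Where 46 per group does reach 80%.** With REF held at 43%:

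| TPA rate | Pooled formula | Exact chi-squared |
|---|---|---|
| 70% | 75.1% | 74.3% |
| 71.5% | 79.9% | 79.1% |
| 72% | 81.4% | 80.6% |

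With TPA held at 70%, the REF rate would have to be about 41% (pooled formula 81.0%).

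**The case against.** Four points can be made for the plan.

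- **Rounding.** The proportions are printed as whole percentages, and the 43% is an estimate whose unrounded value is not shown. With 70.4% versus 42.5%, which would print as 70% and 43%, the unpooled formula gives 80.3% at 46. This needs both inputs near the edge of their rounding range and the most favourable formula. On the same inputs the pooled formula gives 77.9% and the exact chi-squared test 77.2%. What stands is that the failure of every two-sided formula holds for the inputs as printed.
- **Floors.** The TPA rate is given as 70% or above, and 138 is a minimum. A number said to be required for 70% or more must hold at 70%, however, and the Sample size section ties the power claim to 46 per group.
- **Test for sizing not named.** The Sample size section speaks of return to work during the period, which could point to a time-to-event calculation. On that reading the shortfall is about 2 points, but power is still below 80%.
- **The 67% belongs to a test the plan does not name.** This is fair. The finding rests on about 75%; the lower figure applies only if a corrected or exact test is used.

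The consequences are also limited. No estimate, test or error rate under the null changes, and the planned confidence intervals will show the precision directly. That bears on the weight of the point, not on whether the sentence is correct.

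**Conclusion.** The concern holds. For the printed inputs and the named test, the power is about 75% (75.1% by the pooled formula, 74.3% exact), at least 5 points below the claim. The matching number for 80% power by the pooled formula is 52 per group, 6 more than planned. The conclusion takes 70% and 43% as exact, two equal groups of 46 all analysed, a two-sided 5% level and an uncorrected chi-squared test of TPA against REF. Changing the formula or allowing for rounding moves the figure by a few points but does not bring the named test to 80%. The shortfall is moderate and does not invalidate the trial; the power statement is nevertheless incorrect and should not stand.

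**What to change.** Replace the power statement in the Sample size section with wording such as: 46 participants per group give about 75% power (uncorrected chi-squared test, two-sided alpha 0.05) to detect 70% versus 43% returning to work; 80% power is reached at a TPA rate of about 71.5% to 72% against 43%. Naming the uncorrected test matters because a corrected or exact test would lower the first figure to about 67%.

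If the 46 came from other inputs or software settings, the sponsor should state them, since those printed do not yield it. Keeping the 80% claim at 70% versus 43% would instead mean 52 per group, 3 × 52 = 156 in all; restating the power avoids that.

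The cost is one sentence and a less favourable stated power. The planned number of participants and the analysis do not change.

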### Statistical analysis

All participants who receive a group allocation will be included for efficacy and feasibility (intention-to-treat population). The primary outcome, differences across the groups in the proportion of participants who are not sick-listed at 3 and 12 months, will be calculated using a Chi-squared test (and 95 confidence intervals). Also, the rate of return to work at 3 months (co-primary outcome measure), will be calculated based on the number of days with sickness absence as recorded by the Department of Financial Security in Sonderborg Municipality. We will compare the time on sick leave across the groups using the Kaplan-Meier method and report the median time on sick leave with a 95% confidence interval. A Cox proportional hazard model will be used to measure the effectiveness of TPA and CPSMP relative to REF, which will be reported as hazard rate ratio (HRR) with a 95% confidence interval. Participant characteristics that vary amongst the three groups at baseline will be included in a multivariate Cox proportional hazard model to control for their potential confounding effect.

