## Methods

### Study design

This study is a parallel randomised single-blind controlled trial. It will evaluate the efficacy of TPA including general aerobic training and specific strength training versus REF on return to work. CPSMP will be included as an active comparator as illustrated in Figure 1.

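### The primary chi-squared test names no contrast and reads as a three-group test, whereas the trial is sized on TPA versus REF and its aim is set against REF

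*Protocol article*

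**What the plan says.** - **Primary analysis** (protocol article, Statistical analysis): "differences across the groups in the proportion of participants who are not sick-listed at 3 and 12 months, will be calculated using a Chi-squared test", with confidence intervals. No pair of groups is named. The same section later refers to three groups when it describes baseline adjustment. For the Cox model it does name contrasts: TPA and CPSMP, each relative to REF.
- **Sample size**: the calculation uses one pair of rates, "Assuming 70% or more of the participants in the TPA group and 43% of the participants (estimate based on previous data) in the REF group", over the 3-month observation period. It gives 46 per group for more than 80% power at two-sided alpha 0.05. No CPSMP rate is given, and the section adds that "this study will not be powered with a pre-hoc assumption of superiority or non-inferiority between the TPA and CPSMP groups".
- **Study design**: "It will evaluate the efficacy of TPA including general aerobic training and specific strength training versus REF on return to work", with CPSMP as an active comparator.
- **Background, closing paragraphs**: the aim is wider, namely TPA or CPSMP, each against REF. The hypothesis is that TPA does better in the short term and that CPSMP may act in the long term.

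**The concern.** The test and the question do not match. An across-group test asks whether any of the three proportions differ. It can be significant because CPSMP differs from REF, or because TPA differs from CPSMP, a contrast for which the plan disclaims power. It can also miss a real TPA versus REF difference when CPSMP falls between the two, because it spends a second degree of freedom. The primary p-value would then not be evidence for the comparison on which the trial was sized, and its power would depend on a CPSMP rate that the plan does not give.

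**Working it through.** **Inputs.** From Sample size: TPA 0.70 (the lower bound of the assumption), REF 0.43, 46 per group, two-sided alpha 0.05. The CPSMP rate is not stated, so it is an assumption and is varied.

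**Step 1: the plan's own figure, TPA versus REF.** Normal approximation with pooled variance under the null; mean rate (0.70 + 0.43)/2 = 0.565.

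- Null standard error: √(2 × 0.565 × 0.435 / 46) = 0.1034
- Alternative standard error: √((0.70 × 0.30 + 0.43 × 0.57) / 46) = 0.0995
- Power: Φ((0.27 − 1.96 × 0.1034) / 0.0995) = Φ(0.68) ≈ 75.1%

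Exact enumeration of the uncorrected chi-squared test gives 74.3%. For 80% power the same formula needs 52 per group. Other two-sided variants need 49 (unpooled variance), 52 (arcsine) or 59 (continuity-corrected). None gives 46, so the stated figure is not reproduced.

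**Step 2: the three-group test at 46 per group.** The 2-df Pearson statistic is approximately noncentral chi-squared with λ = n Σ(pᵢ − p̄)² / (p̄(1 − p̄)), where p̄ is the mean of the three rates. The critical value is 5.99.

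Example with CPSMP at 0.50: p̄ = 0.5433, Σ(pᵢ − p̄)² = 0.03927, p̄(1 − p̄) = 0.2481, so λ = 46 × 0.03927 / 0.2481 = 7.28 and power is 67.4%.

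| Assumed CPSMP rate | λ | Power, noncentral chi-squared | Power, simulation (400,000 runs) |
|---|---|---|---|
| 0.43 | 8.96 | 76.9% | 78% |
| 0.50 | 7.28 | 67.4% | 69% |
| 0.565 | 6.82 | 64.3% | 65% |
| 0.60 | 7.02 | 65.7% | 66% |
| 0.65 | 7.87 | 71.0% | 71% |
| 0.70 | 9.40 | 78.9% | 79% |

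By the approximation, power reaches 80% only when the CPSMP rate is at or below about 0.41 or above about 0.705. For 80% power with CPSMP between 0.43 and 0.70, the 2-df test needs 48 to 65 per group.

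**Step 3: what a rejection would mean.** Set TPA = REF = 0.43 and CPSMP = 0.70. The across-group test rejects in about 78% of simulated trials although TPA has no effect. The pairwise TPA versus REF test rejects in about 5%.

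**Step 4: how often the two tests would disagree.** With TPA 0.70, REF 0.43 and CPSMP at 0.50 to 0.60, about 9-11% of simulated trials have a significant TPA versus REF test and a non-significant across-group test.

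**The case against.** **The three-group test is inferred.** The section states no degrees of freedom and no 3 × 2 table. The promised confidence intervals suit pairwise differences, since a three-group test has no single effect to put an interval around, and the Cox contrasts in the same section are against REF. This stands as a caution. Even if pairwise tests were meant, the text does not say which of them is primary, and the same repair applies.

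**The aim is wider than TPA versus REF.** This stands. The Background also sets CPSMP against REF, so an across-group test is not irrelevant to the aims. It still isolates neither contrast with REF.

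**A condensed article may leave contrasts to the full plan.** This holds for detail, but here the article does state a test for the primary outcome, and that test does not match its own sample-size contrast.

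**The power loss is not simply due to three groups.** A reader might infer that the three-group test is what brings the trial below its stated power, and that naming the contrast would put this right. The document's figures do not support that. The pairwise test also falls short, at about 75%. When CPSMP equals REF or TPA, the 2-df test has slightly more power than the pairwise test, and outside about 0.41 to 0.705 it exceeds 80%, though not for the contrast of interest. All figures take TPA at exactly 70%, and the plan allows for more.

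**Conclusion.** The concern holds in a limited form. As worded, the primary test does not identify the comparison on which the trial is sized, and a significant result would not establish that TPA differs from REF. That does not depend on any power figure, only on reading the test as a three-group one, which is natural but not certain.

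The power cost is conditional. If the CPSMP rate is about 50% to 65%, the three-group test has about 65-71% power against 74-75% for the pairwise test, a loss of roughly 3 to 10 points. A CPSMP rate below TPA at 3 months fits the short-term hypothesis, but the document gives no value. The gap between about 75% and the stated figure above 80% belongs to the sample-size calculation and is a separate error.

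**What to change.** In Statistical analysis:

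1. Name TPA versus REF as the primary contrast for the proportion not sick-listed, reported as a risk difference with 95% confidence interval and a two-group chi-squared test.
2. Make 3 months, the time point on which the trial is sized, the main analysis, and keep 12 months with a stated role.
3. Report CPSMP versus REF as a separate contrast with its own confidence interval, in line with the aim.
4. Make any three-group test descriptive.

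This costs a few sentences and needs no extra data. It does not restore power above 80%. Separately, Sample size should restate the power as about 75% at 46 per group; 80% would need 52 per group, or 3 × 52 = 156 in total instead of 138.

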#### Tailored Physical Activity-group (TPA)

This intervention group will receive TPA in addition to health guidance.

TPA sessions will be performed in teams of up to 10 participants and include a standardised combination of aerobic fitness and strength training for 50 minutes 3 times per week over 10 weeks supervised by a physiotherapist at the Health Care Centre in the Sonderborg Municipality. The participants will be referred to one of three standardised training programmes based on their primary region of musculoskeletal problems (neck and shoulder pain, arm and/or hand pain, lower back pain).

The three standardised training programmes all start with 5 minutes warm up during which the participants will gradually increase their heart rate (HR) followed by aerobic fitness training for 20 minutes at intensities ranging from 50% with a progression up to 80% heart rate reserve. During the following weeks, training will be tailored to the participant’s current training status and pain problems [19].

For the warm up and the aerobic fitness training, the participants can choose between ergometer cycling, rowing, stepping or cross training. The choice is taken after consultation with the physiotherapist taking into consideration the participant’s current musculoskeletal troubles and general health. The relative workload will be estimated based on the known relationship between HR and oxygen uptake, i.e. relative workload = (working HR – resting HR)/(maximum HR – resting HR). Resting HR is set at 70 beats per minute and maximum HR is estimated at 208 – (0.7 × age) [20]. HR is monitored during each training session to ensure an optimal training intensity.

Participants with pain that is related to the upper body and the neck are referred to high-intensity strength training in modified programmes [9,10]. The programme for neck and shoulder pain contains five different dumbbell exercises; one-arm row, shoulder abduction, shoulder elevation, reverse flies and upright row. The participants with pain primarily located in the arm and/or hand region will participate in a programme with five different dumbbell exercises: front raise, shoulder abduction, reverse flies, shoulder elevation and wrist extension.

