#### “Chronic Pain Self-Management Program”-group (CPSMP)

This active comparator group will receive CPSMP in addition to health guidance. CPSMP is developed for people who have a primary or secondary diagnosis of chronic pain. Pain is defined as being chronic or long term if it has lasted for longer than 3 to 6 months.

The CPSMP is a weekly workshop of 2.5 hours for 6 weeks in the Health Care Centre in Sonderborg. Workshops will be facilitated by two trained leaders, at least one of whom is a non-health professional who suffers from chronic pain.

Topics covered in the teaching sessions will include: (1) techniques to deal with problems such as frustration, fatigue, isolation, and poor sleep, (2) appropriate exercise for maintaining and improving strength, flexibility, and endurance, (3) appropriate use of medications, (4) communicating effectively with family, friends, and health professionals, (5) optimal nutrition, 6) pacing activity and rest, and (7) how to evaluate new treatments.

Additionally, there will be homework in the form of working with plans for action and reading a course book. The participants will take part in courses with group sizes of 12–18 persons and the teaching method will be based on the concept of self-efficacy.

The process used during the teaching programme is supposed to be the key element that makes the programme effective. Classes are highly participative and mutual support and success will build the participants’ confidence in their ability to manage their own health, maintain activities and fulfill their life expectations. The CPSMP will not conflict with existing programmes or treatment and is designed to enhance the regular treatment. The programme offers the participants new skills in order to manage initiatives for promoting their health, as well as to help them keep active in their daily life [21].

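### TPA and CPSMP are delivered in groups, but the planned chi-squared and Cox analyses treat all participants as independent, so intervals against REF are too narrow if outcomes correlate within a team or course

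*Protocol article*

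**What the plan says.** All places are in the Methods of the protocol article.

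- **Delivery of TPA:** "TPA sessions will be performed in teams of up to 10 participants", three times a week for 10 weeks under a physiotherapist.
- **Delivery of CPSMP:** "courses with group sizes of 12–18 persons", weekly for 6 weeks with two leaders. The same section describes the teaching process as what is supposed to make the programme work, and refers to participative classes and mutual support.
- **Delivery of REF:** the individual 1.5-hour health guidance that all arms receive, and nothing more.
- **Randomisation:** by individual, in blocks of 3 and 6.
- **Primary analysis:** the difference in proportions at 3 and 12 months "will be calculated using a Chi-squared test (and 95 confidence intervals".
- **Co-primary analysis:** Kaplan-Meier estimates, and Cox hazard rate ratios with 95% intervals for TPA and CPSMP against REF. The only adjustment named is for baseline characteristics that differ between the groups.
- **Sample size:** "a sample size of 46 individuals in each group will be required" for "greater than 80% statistical power" ("two-sided, alpha = 0.05"). No ICC or design effect appears.

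**The concern.** This is a partially nested design: two arms have participants who share sessions, peers and instructors, and the third does not. A chi-squared test and an ordinary Cox model compute the variance as if nobody shared anything. If people in the same team or course have more similar return-to-work outcomes than people in different ones, the variance of the TPA or CPSMP proportion is larger than the formula gives, while the REF variance is right. The planned interval for each comparison with REF is then too short and its p-value too small. For CPSMP the article itself describes a group mechanism, so some positive correlation is plausible. The comparisons with REF are the stated aim of the trial, so the reported precision of its main results is at stake. The point estimates are not affected.

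**Working it through.** **Inputs from the article.** 46 per arm; two-sided 5% level; return to work 70% (TPA) and 43% (REF); TPA teams up to 10; CPSMP courses of 12–18; eleven recruitment sequences; interventions start within one week of baseline and randomisation.

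**Assumed.** ICC 0.01, 0.02 and 0.05, because none is given. Arms of equal size, clustering in the active arm only, and pairwise comparison with REF.

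**Step 1: the plan's own figure, without clustering.** With p̄ = 0.565 and d = 0.27, the pooled formula gives

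n = [1.96·√(2·0.565·0.435) + 0.842·√(0.70·0.30 + 0.43·0.57)]² / 0.27² = (1.374 + 0.568)² / 0.0729 ≈ 51.7, so 52 per arm.

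At 46 per arm power is 75.1% (77.5% with unpooled variance). The stated 46 is therefore not reproduced even with independent data.

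**Step 2: how many trial participants share a group.** 46/11 = 4.2 per arm per sequence. A course of 12–18 filled only with trial participants would need 12/4.2 ≈ 2.9 to 18/4.2 ≈ 4.3 sequences pooled, which fits poorly with a one-week start. The article does not say whether courses also hold people outside the trial. The plausible range for m, the number of trial participants per group, is therefore about 4 up to 10 (TPA) or 18 (CPSMP).

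**Step 3: variance and type I error.** The design effect in the grouped arm is DE = 1 + (m − 1)·ICC. With DE = 1 in REF and equal outcome variance, the variance of the difference is multiplied by R = (1 + DE)/2, the true standard error is √R times the naive one, and the type I error of the nominal 5% test is 2·[1 − Φ(1.96/√R)]. The last column is a beta-binomial simulation of the uncorrected chi-squared test (46 per arm, both rates 43%, 100,000 runs). It gives 4.7% with independent data.

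| Group | m | ICC | DE | √R | Type I, formula | Type I, simulated |
|---|---|---|---|---|---|---|
| Either arm, one sequence | 4.2 (simulated with 4) | 0.01 | 1.03 | 1.01 | 5.2% | 4.9% |
| | | 0.05 | 1.16 | 1.04 | 5.9% | 5.4% |
| TPA, full team | 10 | 0.01 | 1.09 | 1.02 | 5.5% | 5.0% |
| | | 0.05 | 1.45 | 1.11 | 7.7% | 7.0% |
| CPSMP, smallest course | 12 | 0.01 | 1.11 | 1.03 | 5.6% | 5.2% |
| | | 0.05 | 1.55 | 1.13 | 8.3% | 7.9% |
| CPSMP, largest course | 18 | 0.01 | 1.17 | 1.04 | 6.0% | 5.5% |
| | | 0.05 | 1.85 | 1.19 | 10.1% | 9.2% |

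Worked case for m = 18, ICC 0.05: DE = 1 + 17·0.05 = 1.85; R = 2.85/2 = 1.425; √R = 1.19.

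**Step 4: at the planned proportions.** With 70% against 43%, R becomes (0.21·DE + 0.2451)/0.4551. At ICC 0.05 the standard error is 1.10 times the naive one for m = 10, and a nominal 95% interval covers 92.5%. For m = 18 the figures are 1.18 and 90.3%; the 70% is borrowed from TPA because no CPSMP rate is given. For about 4 per group they are 1.04 and 94.1%.

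**The case against.** The strongest points on the other side, and what stands of each:

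- **No ICC is given, and registered sick-list status may correlate little within a course.** The Background says that the person, the company and the municipality influence return to work, and the Study population section expects some participants to be kept from attending. Both would dilute within-group correlation. This stands: the point is conditional, and at ICC 0.01 the simulated type I error stays at or below 5.5% for every group size. A reader might infer that the intervals are certainly too narrow; the documents do not show that.
- **Full courses of trial participants are doubtful.** This stands, by step 2. A reader might infer that the problem lies mainly with CPSMP because its courses are larger. With about 4 trial participants per group in both arms, that contrast largely disappears.
- **Individual randomisation protects the strict null.** If neither programme affects anyone, sharing a course adds no correlation and the test keeps roughly its nominal level. This also stands: the type I figures apply when group effects vary but average to zero. Outside that case, the issue is interval coverage.
- **The analysis section speaks of differences across the groups.** If that means one three-arm test, the pairwise type I errors above do not describe it exactly. They do bear on the separate comparisons with REF.
- **A condensed article may leave a sensitivity analysis to the full plan.** That is fair as regards the remedy. But the article does name its primary methods, and those do not match the delivery it describes.

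**Conclusion.** The point holds in conditional form. The named analyses ignore a grouping that the article itself sets up in two of three arms, and any positive within-group correlation makes the intervals and p-values against REF too optimistic. At an assumed ICC of 0.01–0.05, the true standard error exceeds the naive one by about 1–4% if about 4 trial participants share a group. With full groups of trial participants the excess reaches about 11% for TPA and 19% for CPSMP. The upper figures need both the top of the assumed ICC range and full groups.

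A reader might also attribute the shortfall from the stated 80% power to clustering. Power at 46 per arm is already about 75% with independent data, so that is a separate issue. Clustering would lower it further: on the pooled formula for TPA against REF at ICC 0.05, to 71.8% with about 4 per group and 66.2% with teams of 10.

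**What to change.** 1. Record a team or course identifier for each TPA and CPSMP participant. Without it the question may not be answerable later.
2. Keep the planned chi-squared and Cox analyses as primary, and leave the sample size unchanged on this account.
3. Prespecify a sensitivity analysis with each REF participant as a group of one:
   - For the 3- and 12-month differences in proportions, inflate the variance in the grouped arms at ICC 0.01, 0.02 and 0.05, using the actual number of trial participants in each group. Fixed values avoid relying on an ICC estimated from very few groups.
   - For the Cox hazard rate ratios, use a cluster-robust variance or a shared frailty by team or course, because an ICC on the binary scale does not carry over directly to a hazard ratio. State the small number of groups as a limitation: with full groups, about 46/10 ≈ 5 TPA teams and 46/18 to 46/12 ≈ 3–4 CPSMP courses.
4. Report these intervals beside the primary ones and qualify any TPA–REF or CPSMP–REF conclusion that changes. Do not set a pass/fail rule at ICC 0.05, since the range is a convention.

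The cost is one data field and a short additional analysis. The downside is wider sensitivity intervals (about 1–19% over the cases above) and dependence on a conventional ICC range.
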